## Abstract

**Background:**

Type 1 diabetes (T1D) has been increasing globally over the past three decades. Self-monitoring of blood glucose is a challenge in both developed as well as developing countries. Self-management guidelines include maintaining logbooks for blood glucose, physical activity, and dietary intake that affect glycated hemoglobin (HbA1c) and a multitude of life-threatening acute complications. Innovative, cost-effective interventions along with beneficial lifestyle modifications can improve home-based self-monitoring of blood glucose in T1D patients. The overall objective of this study is to evaluate the relationship between maintaining log books for blood glucose levels, reinforcement by e-messages, and/or daily step count and changes in HbA1c.

**Methods/design:**

A randomized controlled trial will enroll participants aged 15 years and above in four groups. Each group of 30 participants will be working with a newly designed standard log book for documenting their blood glucose. The first group will be entirely on routine clinical care, the second group will be on routine care and will receive an additional e-device for recording step count (fit bit), the third group will receive routine care and daily motivational e-messages to maintain the log book, and the fourth group along with routine care will receive an e-device for measuring step count (fit bit) and e-messages about maintaining the log book. Patients will be enrolled from pediatric and endocrine clinics of a tertiary care hospital in Karachi. All groups will be followed up for a period of 6 months to evaluate outcomes. Log book data will be obtained every 3 months electronically or during a patient’s clinic visit. HbA1c as a main outcome will be measured at baseline and will be evaluated twice every 3 months. A baseline questionnaire will determine the socio-demographic, nutritional, and physical activity profile of patients. Clinical information for T1D and other co-morbidities for age of onset, duration, complications, hospitalizations, habits for managing T1D, and other lifestyle characteristics will be ascertained. Behavioral modifications for maintaining daily log books as a routine, following e-messages alone, fit bit alone, or e-messages plus using fit bit will be assessed for changes in HbA1c using a generalized estimated equation.

**Discussion:**

The proposed interventions will help identify whether maintaining log books for blood glucose, motivational e-messages, and/or daily step count will reduce HbA1c levels.

**Trial registration:**

ClinicalTrials.gov, NCT03864991. March 6, 2019.

## Background

Type 1diabetes (T1D) is an autoimmune disease in which insulin-producing beta cells in the pancreas are destroyed by the human body pathologically, preventing the body from being able to produce enough insulin to adequately regulate blood glucose levels. The diagnosis is based on clinical factors (age, lack of obesity, and insulin resistance), low C-peptide levels, and insulin antibodies. Substantial destruction of insulin-producing beta cells in the pancreas of T1D patients means that rigorous blood glucose monitoring for adjustment of insulin dosage is required on a daily basis [1].

T1D occurs mostly in the pediatric and adolescent age groups with patients presenting with a hyperglycemia and/or diabetic ketoacidosis episode. Such episodes are also the most common life-threatening adverse effects following diagnosis resulting from suboptimal treatment if insulin dosage is not adjusted and blood glucose is not monitored on a daily basis. The incidence of T1D has been increasing over the past three decades [2]. Management of T1D is a big challenge in resource-constrained low to middle income countries due to the need for daily self-monitoring of blood glucose (SMBG) levels and timely entry of these in a log book [3, 4]. SMBG is an invaluable method for monitoring glycemic status; current guidelines recommend its use in all patients with T1D, type 2 diabetes mellitus (T2DM), or any other forms of diabetes (e.g., gestational diabetes) that require administering multiple subcutaneous insulin injections [5]. A study of children and adolescents with T1D showed that an increased daily frequency of SMBG was significantly associated with lower HbA1c levels (0.2% per additional test per day) along with the added benefit of fewer acute complications such as ketoacidosis [6]. Use of innovative mobile phone applications and regular SMBG have been shown to increase compliance with proposed treatment regimens [7].

Taking an extra 1000 steps per day can help to reduce the risk of cardiovascular events significantly in T1D patients [8]. A wireless wearable e-device accompanied by an application (called the fit bit app) tracks step count by recording data in a mobile phone application [9–11]. Studies conducted in Pakistan report non-adherence of T1D patients to dietary advice (58.5%), physical activity recommendations (42.3%), and prescribed insulin regimens (88.1%), with staggering rates of complications such as diabetic acidosis due to suboptimal treatment [12, 13]. HbA1c levels acts as an indicator of glycemic control and correlate with the occurrence of complications [14]. However, HbA1c levels do not indicate the daily variability of blood glucose. The risk related to daily fluctuation of blood glucose levels can be assessed by a devised method [15, 16]. This study proposes to study maintenance of log books for blood glucose levels and whether motivational e-messages and/or using an e-device for measuring step count, alone or together, can potentially help reduce HbA1c levels in T1D patients. In addition, it will explore any effect of increasing step counts on daily blood glucose levels and reduction in acute complications by maintenance of log books for blood glucose.

### Rationale

Adequate glycemic control along with a healthy lifestyle are associated with improved health outcomes and lower morbidity and premature mortality in diabetes patients. Therapeutic insulin regimens need to be strongly regulated during the adolescent period to prevent complications in T1D patients [17]. Adolescents with poor glycemic control had greater proportions of diabetic retinopathy and micro- and macro-albuminuria than patients who maintained their HbA1c levels in a strict therapeutic range [17]. Adherence to management protocols and insulin regimens had an inverse association with occurrence of acute complications in several studies on T1D patients [18, 19]. Poor compliance with or no insulin regimen were directly associated with severity of diabetic ketoacidosis in T1D patients in Pakistan, who needed longer hospital stays [20]. Family-centered care empowering family members to maintain a blood glucose level record sheet, insulin dosage recording, physical activity, and a meal plan resulted in significant differences in behavior and supervision of adolescents with T1D [21]. At the regional level management of T1D is a big challenge as physicians tend not to adhere to the international treatment guidelines regularly [4, 9]. Several e-devices are available to monitor physical activities and these have been studied globally for use by diabetic patients [6, 9–11]. Most of the studies using and e-device for improving patient outcomes have been performed on T2D patients due to its high prevalence [22–27]. T1D patients are usually in the pediatric age bracket and have increased chances of severe acute complications; therefore, multifaceted approaches involving patients, parents, families, doctors, and stakeholders are required for optimal T1D management [12, 13, 17, 20, 28]. A study done in India assessed the reliability of SMBG logs compared with glucometer memory in children with T1D and the impact on glycemic indicators. Children who maintained accurate records (aged 11.54 ± 4.05 years) had decreased HbA1c levels (from 10.79 ± 2.61% to 7.99 ± 0.84%) and those participants who kept inaccurate records had decreased HbA1c levels (from 10.74 ± 2.60% to 9.01 ± 2.33% over a period of 4 months (*p* < 0.002) [6]. There is a dearth of literature on testing of basic, cost-effective interventions to improve home-based and self-monitoring of blood glucose levels and management of insulin regimens with added beneficial lifestyle modifications. Therefore, the proposed study will record adherence to standard protocols for maintenance of SMBG records by patients, checking HbA1c level every three months, and maintaining an insulin dosage record on a daily basis to determine if these lead to reduction in acute complications in T1D patients, thereby reducing their illness-associated mortality and morbidity.

#### Study purpose

The purpose of this formative research using a factorial design is to evaluate the relationship between maintaining log books for daily blood glucose, reinforcement by e-messages, and/or daily step count using a fit bit device and changes in HbA1c in T1D patients visiting Aga Khan University (AKU) endocrine clinics. In addition, episodes of acute complications will be compared in T1D patients in each intervention arm over a period of 6 months.

#### Study objectives

Primary objectives:
To determine the effect of daily mobile phone messages for maintenance of log books and self-monitoring of blood glucose levels on HbA1c levels in T1D patients in comparison to routine clinical careTo determine the relationship of wearing an e-device for daily step count with blood glucose levels and changes in HbA1c in T1D patients in comparison to routine clinical care

Secondary objectives:
To compare the acute complications of T1D in all groups over a period of 6 monthsTo compare the variability of daily blood glucose measurements using an average daily risk range method

## Methods/design

### Study design

A factorial design will help to study lifestyle changes for self-management of T1D (Fig. 1). A randomized controlled method will enroll patients in a predefined sequence, assigning them in four groups. All groups will be working with a newly designed standard log book for documenting records for blood sugar and routine insulin dosage and care as provided by doctors, nurses, and nutritionists. The first group will all receive routine care follow-up, the second group will receive an additional e-device for measuring step count (fit bit), the third group will receive routine care and e-messages as reminders to maintain a daily log book, and the fourth group will receive an e-device for measuring step count (fit bit) and e-messages about maintaining the log book, blood glucose levels, and step count in addition to routine care. All groups will be followed up overall for a period of 6 months. HbA1c as a main outcome will be measured at least three times, at baseline, and then once every 3 months.

**Fig. 1 Fig1:**
[figure not shown]
Flow diagram

### Study setting

The study will be conducted in pediatric and adult endocrinology clinics at Aga Khan University (AKU) Karachi, where records of patients are maintained electronically using a heath information management system (HIMS) as well as individual medical record files. Patients under the care of consultant endocrinologists who fulfill the inclusion criteria will be enrolled.

### Study participants

We plan to include all T1D patients aged more than 14 years visiting pediatric and endocrine clinics of AKU. We plan to enroll patients who have been diagnosed with T1D at least 6 months prior to the enrollment.

### Enrolment procedure

Informed consent will be obtained from patients aged 18 or more years and assent from patients aged less than 18 years with additional consent from parents.

### Inclusion and exclusion criteria

Males and females diagnosed with T1D and aged more than 14 years who present to pediatric and endocrine clinics of AKU and have a smart phone or a family member with a smart phone, such as parents or elder sibling, are eligible to participate in the study. However, patients using an “insulin pump” will be excluded. Patients with complicated health conditions such as neurodevelopmental delay and thalassemia will be excluded. Furthermore, patients already using any kind of authentic e-device for measuring step count and/or physical activity will also be excluded from the study.

### Randomization

Unique allocation numbers will be designated by the Clinical Trail Unit (CTU) with computer-generated block randomization, using a block size of four. Sealed opaque identical envelopes will be received by the principal investigator (PI) from the CTU in an order that will be followed to enroll study participants in all four groups. The data collector will be instructed to assign allocated numbers to participants in sequential order as they are enrolled. Upon opening the envelope, the group, A, B, C, and D, will be revealed to the data collector and items related to the appropriate group will be explained to the study participant. Group A will be told to follow routine care, group B will receive an additional e-device for measuring step count (fit bit) and the data collector will download the associated application onto the participant’s cell phone, group C will receive routine care and e-message reminders from the data collector to maintain a daily log book, and group D will receive routine care as well as an e-device for measuring step count (fit bit) together with the associated application (downloaded onto the participant’s cell phone by the data collector) and e-messages from the data collector as reminders to maintain their log book, blood glucose levels, and step count.

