### Sample size and sampling technique

Overall, 120 patients with T1D will be randomized into four equal groups for evaluating changes in HbA1C using multiple measurements at multiple time points. Thirty patients in each group will be required in order to achieve 80% power for a two-sided level of significance of 5%, using a standard deviation of change in HbA1c between 1.1% and 2.3% and absolute difference of at least 2% expected over a period of 6 months within a group from baseline as well as when compared across the four groups [29]. A consecutive sampling technique will be used to enroll participants visiting AKU pediatric and endocrinology clinics and fulfilling the eligibility criteria.

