### Ethical considerations

Study participants will be asked to provide informed, written assent/consent prior to participation in this study. Appropriate assent/consent will be obtained by trained data collectors during face to face interviews; the data collectors will also make contact via phone call. Confidentiality of participants will be maintained throughout the follow-up. Study participants will be interviewed in areas separate to the clinical examination room and identification codes will be used to manage the data. This study will not impose any risk or discomfort on any patient or their parents, except for requiring their valuable time; however, this study intends to introduce beneficial lifestyle changes for improving the management of T1D by young adolescents and adults. Ethics approval from Aga Khan University Ethical Review Committee (AKU-ERC) was provided prior to initiating this study.

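### One fixed block size of four for four unblinded groups could let enrolling staff predict upcoming allocations, up to 30 of 120 with certainty

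*Protocol article*

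**What the plan says.** The Randomization section of the protocol article gives one method and one block size: "computer-generated block randomization, using a block size of four". Sample size and sampling technique fixes the ratio: "120 patients with T1D will be randomized into four equal groups".

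Concealment rests on envelopes: "Sealed opaque identical envelopes will be received by the principal investigator (PI) from the CTU in an order that will be followed". Numbers are given out in order: "The data collector will be instructed to assign allocated numbers to participants in sequential order as they are enrolled". The result then becomes known to the same role: "Upon opening the envelope, the group, A, B, C, and D, will be revealed to the data collector".

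Delivery is visible as well. For group B, "the data collector will download the associated application onto the participant’s cell phone"; group D has the same arrangement. For messages, "group C will receive routine care and e-message reminders from the data collector to maintain a daily log book", and group D also receives messages. The article does not use the term open-label, but neither a wearable device nor messages sent by the collector can be hidden from the collector.

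Ethical considerations assigns recruitment to this role too: "Appropriate assent/consent will be obtained by trained data collectors during face to face interviews". Nowhere does the article describe varying block sizes, or say that the block size is kept from the staff who enrol.

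**The concern.** With four groups in a 1:1:1:1 ratio, a block of four is simply an ordering of A, B, C and D. Someone who has seen the first three results in a block knows the fourth before the envelope is opened. After two results, only two groups remain. Opacity and sealing do not help, because the prediction comes from past results and not from the envelope.

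This matters because the role that sees the results also conducts the consent conversation. If the next group is known or suspected, that knowledge can affect whether an eligible patient is approached, when, and how the trial is presented. The groups could then differ at entry in characteristics such as motivation, which plausibly bears on log-keeping and HbA1c. Intention-to-treat analysis does not repair such a difference, because it relies on allocation having been unpredictable at entry. Laboratory measurement of HbA1c protects the measurement of the outcome, not the comparability of the groups.

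**Working it through.** **Inputs.** Block size 4 and groups A to D (Randomization); N = 120 in four equal groups (Sample size and sampling technique); recruitment from October 29, 2018 to about March 31, 2020 (Trial status).

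**The plan's own figure.** 120 / 4 = 30 complete blocks. One patient per group per block × 30 blocks = 30 per group, which agrees with the stated group size.

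**Predictability if one person knows the block size and sees every result.** All 24 orderings of A, B, C and D are possible. The chance of a correct best guess depends only on the position in the block:

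| Position | Groups still possible | Chance of a correct guess | Allocations out of 120 |
|---|---|---|---|
| 1 | 4 | 1/4 | 30 |
| 2 | 3 | 1/3 | 30 |
| 3 | 2 | 1/2 | 30 |
| 4 | 1 | 1 | 30 |

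- Certain in advance: 30 / 120 = 25%.
- Narrowed to two groups: another 30.
- Average success: (1/4 + 1/3 + 1/2 + 1) / 4 = 25/48 = 52.1%, or 62.5 of 120.
- Device or no device: in one third of blocks the first two results are both device groups or both non-device groups, so the device status of the third is already settled. That adds 30 / 3 = 10, giving 30 + 10 = 40 of 120 allocations with device status known in advance.

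**Several collectors who do not share results.** Assume K collectors draw from one list, each patient being equally likely to fall to any of them. A collector is certain of the fourth allocation only if the same person handled all four patients in that block. The probability is K × (1/K)^4 = (1/K)^3. Certain allocations are then:

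- K = 1: 30 × 1 = 30 of 120.
- K = 2: 30 × 1/8 = 3.75 of 120.
- K = 3: 30 × 1/27 = 1.1 of 120.

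The article gives neither K nor whether results are shared, so the range is about 1 to 30 of 120.

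**Pace.** The recruitment period is 519 days, about 74 weeks. 120 / 74 is about 1.6 patients per week, so a block lasts about 4 / 1.6 = 2.5 weeks. That is short enough to follow from memory.

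**Effect of mixed block sizes.** These results come from 500 simulated sequences of 120. Sizes were drawn with equal probability, and the guesser knew the set of sizes, saw every result and updated by Bayes' rule:

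| Block sizes | Certain in advance | Best-guess success |
|---|---|---|
| 4 only (current plan) | 25% (30 of 120) | 52% |
| 4 and 8 | about 7% (about 9 of 120) | about 49% |
| 4, 8 and 12 | about 3.5% (about 4 of 120) | about 46% |

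The first row reproduces the exact values above. Mixing removes most of the certainty, but only a little of the guessing advantage when the set of sizes is known.

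**The case against.** The strongest reply is that full predictability is a worst case. Ethical considerations speaks of data collectors in the plural, and Study setting covers both pediatric and adult clinics, so one person may not see the whole sequence. No section says that collectors are told the block size. Randomization has the envelopes go to the principal investigator and implies, without stating it, that the collector opens them. It has the collector sending messages, whereas Follow-up and other procedures gives that task to trained staff. These points stand, and they are why the size has to be given as a range.

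Second, Sample size and sampling technique prescribes consecutive sampling, which if followed leaves less room to choose whom to approach. This also stands in part. It does not fully settle the matter, because timing and the consent conversation remain with the collector, and Follow-up and other procedures has clinic schedules shared a day ahead.

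Third, Data analysis adjusts for socio-demographic, clinical, nutritional and physical activity variables. That may reduce imbalance in what is measured. Motivation is not among the assessments in Table 2, so adjustment cannot be relied on to remove it.

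Fourth, a guessing rate is not an estimate of bias in HbA1c. That is correct, and the document gives no basis for such an estimate.

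Finally, tying a participant to a number before opening may already be practice, since numbers are assigned in sequence at enrolment, and an article may leave such detail to the full protocol.

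**Conclusion.** The weakness is real but conditional. As written, a single block size of four for four equal, unblinded groups could allow the staff who take consent to predict upcoming allocations despite sealed envelopes. The upper end is 30 of 120 allocations certain, 30 more narrowed to two groups and 52% of best guesses correct. It requires one collector, or collectors who share results, with knowledge of the block size and a running record of the sequence. With two or three collectors enrolling at random and not sharing, certain predictions drop to about 4 or 1 of 120.

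A reader might infer that the data collector does know every fourth allocation, or that patients were steered into particular groups. The document supports neither. It does not say that collectors are told the block size, how many there are or whether they share results, and nothing in it indicates manipulation. What it shows is a stated rule that leaves allocation open to prediction. Because the remedy is cheap, the rule is worth changing for any part of the sequence still unused.

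**What to change.** For envelopes not yet opened:

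1. The Clinical Trial Unit issues a new sequence from randomly mixed block sizes that are multiples of four, for example 4, 8 and 12.
2. The sizes are withheld from the principal investigator and the data collectors until recruitment ends. This is essential: even with the 4, 8 and 12 mix, someone who knew the set of sizes would still guess correctly about 46% of the time.
3. Consent and baseline data are completed, and the participant identifier is written on the envelope, before it is opened.

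The Unit already generates the sequence, so the cost is one reissue of envelopes and no extra staff. The downside is a possible final imbalance of a few patients per group. A block of 12 holds three of each group, so stopping inside one can leave two groups up to three apart, and interrupting a current block of four can add one more. The change has no effect on allocations already made, and the document does not say how many those are.
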